## Abstract

**Objective:**

Ketamine, an N-methyl D-aspartate (NMDA) receptor antagonist, can promote rapid action in the management of individuals with treatment-resistant depression (TRD) at sub-anesthetic doses. However, few studies have investigated the long-term use of ketamine administered intravenously (IV) and intranasally (IN). We report the design and rationale of a therapeutic trial for assessing the efficacy, safety, and tolerability of repeated-dose intramuscular (IM) ketamine vs. active treatment (escitalopram and aripiprazole) in TRD patients.

**Methods:**

A comparative, parallel-group, randomized double-blind trial assessing the efficacy, safety, and tolerability of acute (4 weeks) and maintenance (24 weeks) use of IM ketamine (0.75 mg/kg) vs. active control (escitalopram 15 mg and aripiprazole 5 mg) in individuals with moderate-severe intensity TRD (no psychotic symptoms) with or without suicide risk will be conducted. Patients with TRD (18–40 years) will be randomized and blinded to receive ketamine IM or active treatment at a 1:1 ratio for 4 weeks (active treatment) and 24 weeks (maintenance treatment). Subjects will be assessed using clinical scales, monitored for vital signs (VS) after application of injectable medication, and undergo neuropsychological tests. The primary outcome will be changed on the Montgomery-Åsberg Depression Rating Scale (MADRS) during the course of the trial. The study is in running.

**Results:**

This study can potentially yield evidence on the use of IM ketamine in the treatment of depressive disorders as an ultra-rapid low-cost therapy associated with less patient discomfort and reduced use of medical resources, and can elucidate long-term effects on different outcomes, such as neuropsychological aspects.

**Conclusions:**

The trial can help promote the introduction of a novel accessible approach for the treatment of complex disease (TRD) and also allow refinement of its long-term use.

**Clinical trial registration:**

https://clinicaltrials.gov/ct2/show/NCT04234776, identifier: NCT04234776.

## Introduction

In 2015, an estimated 300 million people had depression (4.4% of the world's population) (1). Depression is a common recurrent serious mental disorder associated with morbimortality and a burden of 50 million years lived with disability (YLD), constituting the mental disease with the highest global disability (2, 3). The economic impact of depression on productivity ran into billions of dollars (presenteeism and absenteeism) in terms of Gross National Product (GDP) (4). The disease is the largest contributor to suicide (some 800,000 deaths/year), a figure which is probably underestimated (5, 6).

Depressive disorders are heterogeneous diseases categorized by international systems of disease classification and whose treatment approaches are well-defined (7–10). However, only 1/3 of patients experience symptom remission after the first intervention (11, 12). Therapeutic goals have changed over time, and include symptoms remission, recovery of function, improvement in quality of life, and cognitive remission, as well as new antidepressants called “atypical”, have been developed in recent decades, such as duloxetine, agomelatine, vortioxetine, among others, in an attempt to optimize therapeutic results (13–15).

A number of definitions of treatment-resistant depression (TRD) exist, but there is a consensus on non-response after the use of 2 or more antidepressants of different classes (with adjustment of adherence, dose, and duration of use) (16, 17). Since the introduction of the concept in 1974, numerous studies have investigated treatment strategies adopting different definitions of the meaning of the illness (18). Treatment-resistant depression accounts for 12–20% of depressed patients and ~20% of TRD cases are staged as chronic, with various unfavorable clinical outcomes and both social and economic impacts (19–21).

Although numerous TRD treatment strategies exist, many interventions have limited efficacy, undesirable side effects and are high cost or inaccessible, besides presenting other barriers to implementation (22, 23). A new effective, less invasive treatment could significantly relieve the suffering and anguish of patients and their families compared to complex interventions for TRD, for example, neurostimulation treatments (24).

The clinical effects of ketamine involve anesthetic, analgesic, antidepressant, and anti-inflammatory actions (25). The drug is derived from phencyclidine and was developed in the 1960s (26). It has two enantiomers: S-ketamine and R-ketamine, with the racemic preparation containing concentrations of 1:1 (27). The drug undergoes hepatic biotransformation by the liver into different metabolites, norketamine being the most important, a product of demethylation by the P450 cytochrome that is excreted by the kidneys (28). Readily distributed by the tissues, including the brain, ketamine is very lipid soluble and exhibits plasma protein binding (12%) with a half-life of around 10 min (29). Ketamine is an N-methyl D-aspartate (NMDA) receptor antagonist with additional weaker actions on sigma receptors, as well as noradrenalin, serotonin, and dopamine transporters among others (30, 31). A signaling cascade may play a role in the regulation, and synaptic plasticity of the mammalian target of rapamycin (mTOR), and in mediating the rapid effects of ketamine (32). Effective, rapid antidepressant effects *via* non-conventional mechanisms represent one of the most important breakthroughs in the field of psychiatry over the last 50 years (33, 34).

Berman et al. carried out the first clinical trial using intravenous (IV) ketamine at a dose of 0.5 mg/kg in a small sample, observing a meaningful reduction on the Hamilton Depression Scale (HAM-D) after 3 days (35). Subsequently, a growing number of methodologically-refined studies (involving single IV applications) were conducted (36–39). A systematic review of 22 studies [randomized clinical trials (RCTs) and non-RCTs] involving 629 participants investigating the role of ketamine [IV 0.5 mg/kg for unipolar depression (UD) and bipolar depression (BD)] found a rapid effect in most of the studies reviewed, observing greatest magnitude of effect in RCTs at 210–230 min post-application (40). In another systematic review, McGirr et al. investigated the efficacy of ketamine (IV 0.5 mg/kg) in the treatment of depressive episodes of 73 individuals in parallel arms and 110 in cross-over designs (34 participants with BD and 149 with UD), where the primary outcome was clinical remission of symptoms at 24 h, 3 and 7 days vs. placebo: results at 24 h [Odds Ratio (OR) of 7.06 and number needed to treat (NNT) of 5], at 3 days (OR of 3.86 and NNT of 6) and, at 7 days (OR of 4 and NNT of 6) (41).

The safety of ketamine has been confirmed for some decades, with anesthetic doses of 4–5 mg/kg intramuscularly (IM) proving effective [93–100% of children (1,022 pediatric cases)] for airways, emesis, or agitation (46). In a small number of patients, the drug can temporarily affect heart rate, and blood pressure and promote myocardial ischemia, although these risks can be attenuated by the use of sub-anesthetic doses and careful patient selection (27, 41, 44, 47). Dissociative states, a common side effect of the drug, are transient (lasting ~40 min, 2 h after use) and are not associated with persistent psychosis or mood swings (48). Of 158 patients given ketamine, 21 (13.3%) withdrew from the study, compared to 10 (7.4%) out of the 135 patients receiving control interventions (OR 1.95, 95%CI 0.86–4.42, *z* = 1.59, *p* = 0.11) (39). Claims that NMDA receptor blocking can cause “brain damage” and that ketamine affects the urinary retract remain the subject of controversy (49). The most common (≥20%) adverse events following the use of the drug include, headache, anxiety, dissociation, nausea, dizziness, and drowsiness on days of the administration, with these effects dissipating within 2 h, while more serious side effects leading to hospitalization or suicide attempts are rare (40, 50, 51). Anti-depressant effects of ketamine are short-lived (days or weeks), although longer-term benefits can be maintained by use of repeat doses, warranting further studies on the prolonged effects of the drug (44, 52). Intranasal (IN) esketamine was approved for use in 2019 by both the U.S. Food and Drug Administration (FDA) and the European Medicines Agency (EMA) (53). Other administration routes have also been investigated: IN, subcutaneous (SC), and oral (54–56).

## Methods

### Design and study populations

A comparative, parallel-group, randomized, double-blind trial is to be conducted involving an anti-depressant intervention. The experimental group (EG) will use the experimental substance [ketamine IM 0.75 mg/kg, oral placebo (morning), and oral placebo (evening)], while the control group (CG) will use an active treatment administered orally [escitalopram 15 mg (morning), aripiprazole 5 mg (evening) and placebo IM]. The study will be carried out by the Institute of Psychiatry of the University of São Paulo Medical School (HCFMUSP), in conjunction with the Center for Mind Health Studies (NUPE) in the Vale do Itajaí, Santa Catarina state, Brazil. The study is called the KETAMIM project and is Registered Under No. NCT04234776 on the www.ClinicalTrials.gov platform. The study phases and methodological aspects comply with the recommendations of the CONSORT (Consolidated Standard of Reporting Trials) statement and with Good Clinical Practice guidelines (GCP) (65, 66). The study is in running.

The study shall entail 5 phases: (1) Dissemination (P0): patients referred by health professionals, dissemination in the press or online media; (2) Pre-treatment (PI): ~2 weeks for the baseline assessment of candidates for study entry; (3) Therapeutic trial (PII): 4 weeks for ketamine use 3 times weekly and of daily oral medications, as well as placebos for both groups, characterizing acute treatment of the disease; (4) Maintenance (PIII): 24 weeks for weekly ketamine use and maintenance of standard treatment and respective placebos; (5) Post-treatment (PIV): 4 weeks for assessing patients after use of ketamine, maintenance oral medication or placebo.

A total of 88 patients with TRD (≥2 failed trials using anti-depressants, plus ECT as an alternative or otherwise) of moderate-severe intensity [according to criteria of Diagnostic and Statistical Manual of Mental Disorders (DSM-5)], and the diagnosis confirmed by the Portuguese version of the clinical interview of the DSM-IV, will be recruited (67). Patients will be block randomized using a computer-generated list into one of the two interventions (1:1 ratio), EG or CG (68). A nurse blinded to the allocation will administer ketamine or saline IM, placebo orally, or the active treatment, respectively.

### Inclusion and exclusion criteria

**The following individuals will be eligible for study inclusion:** Subjects residing in Itajaí valley (Santa Catarina state, Brazil); adults (age 18–40 years) with a primary diagnosis of TRD based on clinical evaluation and confirmed by the SCID-IV [research version (TRD defined as failure of 2–5 clinical trials with anti-depressants including ECT)]; moderate-severe intensity disease [clinical criteria and/or score ≥14 on the Hamilton Depression Rating Scale (17-item HAM-D)]; with no psychotic symptoms; not presenting an imminent risk of suicide (as indicated by clinical evaluation and HAM-D) and/or murder; with anxiety disorders (secondary); with compensated clinical comorbidities and; literate and able to understand the tasks requested (69). Patients and/or legal guardians must be aware of the nature of the study and give consent by signing the Free and Informed Consent form. All patients will undergo a physical and neurological examination, laboratory tests, and an electrocardiogram (ECG) to ascertain their comorbid clinical and/or uncompensated conditions. **The following individuals will be excluded from the study:** Subjects exhibiting imminent risk of suicide, presenting bipolar spectrum disorders or other diagnosed psychiatric conditions (primary); psychoactive substance dependence within the last year; intellectual deficit; allergy to ketamine; and glaucoma. Fertile women must be in use of a clinically acceptable method of birth control [oral contraceptive and/or condom (only unfollowed topic in GCP)]. In the event of clinical doubt regarding pregnancy, a test for beta-human chorionic gonadotropin (βHCG) hormone will be ordered. Patients who become pregnant during the study period will be excluded and referred for obstetric care. The medication wash-out period required before visit 0 will be 1 week for antipsychotics, antidepressants [except fluoxetine (4 weeks)], and for mood stabilizers. No other medications with psychiatric action will be allowed during the study, except for Lorazepam and Zolpidem for patients in the use of a benzodiazepine or hypnotic agent.

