### Measures and outcome variables

The study will assess (given in Table 1):

Sociodemographic variables: gender, marital status, ethnicity, number of children, income, education, and employment.Clinical characteristics over the life course: clinical and psychiatric comorbidities, smoking, family history of mood disorders, prior pharmacological treatment and ECT, number of mood episodes, previous psychiatric admissions, suicide attempts, currently receiving psychotherapy, and history of sexual, or physical abuse.Clinical history: visits to the emergency room, attempted suicides, or psychiatric hospitalizations.The Montgomery-Åsberg Depression Rating Scale (MADRS) (70, 71): will be applied as a primary outcome measure 3× per week for the first month (PII), 1× per week for 6 months (PIII), and 1× per week (PIV) for 1 month.The Hamilton Rating Scale for Depression (HAM-D) (72, 73): will be applied once in PI to assess symptom severity and again 3× per week for 1 month (PII), 1× per week for 6 months (PIII), and 1× per week (PIV) for 1 month.Vital signs (VS): pulse oximetry, heart monitoring, breathing rate, heart rate, and blood pressure will be checked continuously using non-invasive methods. VS to be monitored 3× per week for the 1st month (PII) and 1× week (PIII) for 2 h continuously after completion of each application.Global Clinical Impression (GCI) scale: this will be applied 3× a week for 1 month (PII), 1× week for 6 months (PIII), and 1× week (PIV) to assess disease severity, global improvement of the condition and hence, treatment efficacy (74).Depression Thoughts Scale (DTS): the DTS will be applied at visit one (V-1), V11, and V-39 to assess for thought distortions (75, 76).Clinician-Administered Dissociative States Scale (CADSS): this will provide a measure of the dissociative effects of ketamine and will be applied 3× per week for the 1st month (PII), and 1× per week for 6 months (PIII), ~1 h after application of injections (77).Young's Mania Rating Scale (YMRS): this scale will be employed in this study to assess manic switching as an adverse effect of the medications and applied 3× week for the 1st month (PII) and 1× week for 6 months (PIII), ~1 h after application of injections (78).Brief Psychiatric Rating Scale (BPRS): Sub-item 12 of the scale will be used for detecting the presence of psychotic symptoms arising after application of ketamine, applied 3× week for 1 month (PII) and 1× week (PIII), ~1 h after application of injections (79).Udvalg Kliniske Undersoegelser Side Effect Rating Scale (UKU-SERS): this will be used to determine the presence of side effects of the medications used and will be applied 3× week for the 1st month (PII) and 1× week (PIII) thereafter, around 1 h after application of injections (79).World Health Organization Quality of Life, brief version (WHOQOL-Bref): this scale will be applied at V-1, V-11, and V-35 (80).Sheehan Disability Scale (SDS): this scale will be applied at V-1, V-11, and V-35 (81).

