
**Table 1 T1:** Outcome measurements over time.

**Scales**	**Baseline**	**P1**	**End of P1**	**P2**	**End of P2**	**P3**	**P4**
SCID	x						
MADRS		x		x		x	x
HAM-D	x	x		x		x	x
CGI-S	x	x		x		x	x
DTS	x		x		x		
Physical and neurological exams	x						
Clinical tests and ECG	x						
VS		x		x		x	
UKU-SERS		x		x		x	
BPRS-12		x		x		x	
CADSS		x		x		x	
YOUNG		x		x		x	
WHOQOL-Bref							
SDS	x		x		x		x
Neuropsychological assessment	x				x		

SCID, Structured Clinical Interview for DSM Disorders; MADRS, Montgomery–Åsberg Depression Rating Scale; HAM-D, Hamilton Depression Scale; CGI-S, Clinical Global Impression—Severity; DTS, Depressed Thoughts Scale; VS, Vital Signs; UKU-SERS, Udvalg for Kliniske Undersøgelser Side Effect Rating Scale; BPRS-12, Brief Psychiatric Rating Scale; CADSS, Clinician-Administered Dissociative States Scale; YOUNG, Young Mania Rating Scale; WHOQOL, World Health Organization Quality-of-Life scale; SDS, Sheehan Disability Scale.

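### Pregnancy testing is ordered on clinical doubt only, and pregnancy is not a named exclusion at entry, so an unrecognised early pregnancy could be randomised and dosed

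*Protocol article*

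**What the plan says.** All statements below are in the protocol article, under Inclusion and exclusion criteria unless noted.

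- **Population:** "adults (age 18–40 years) with a primary diagnosis of TRD". The section refers expressly to fertile women and requires them to use contraception (pill and/or condom).
- **Trigger for testing:** "In the event of clinical doubt regarding pregnancy, a test for beta-human chorionic gonadotropin (βHCG) hormone will be ordered". No time point is attached.
- **Exclusions:** the list runs from suicide risk through other primary psychiatric diagnoses and substance dependence, and ends with "intellectual deficit; allergy to ketamine; and glaucoma". Pregnancy is not in it.
- **Conception on study:** "Patients who become pregnant during the study period will be excluded and referred for obstetric care".
- **Baseline work-up of all patients:** a physical and neurological examination, "laboratory tests, and an electrocardiogram (ECG) to ascertain their comorbid clinical and/or uncompensated conditions". The laboratory panel is not itemised. Table 1 (Outcome measurements over time) shows it as "Clinical tests and ECG", marked at baseline only, and has no row for a pregnancy test.
- **Timing:** Design and study populations gives the pre-treatment phase (PI) about "2 weeks for the baseline assessment of candidates for study entry".

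Reasons for withdrawal or termination does not mention pregnancy.

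**The concern.** The protocol treats pregnancy as incompatible with continued participation: a woman found to be pregnant leaves the trial and is referred. The stated entry rule does not look for a pregnancy unless somebody already suspects one. Early pregnancy is often without signs, so a trigger based on doubt misses the case that a screening test is meant to catch.

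At stake is exposure of a woman and fetus to study treatment before anyone knows of the pregnancy. In the experimental arm that is repeated intramuscular ketamine. In the control arm it is daily oral escitalopram and aripiprazole. The first exposure would already have happened when the removal rule took effect.

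**Working it through.** **Step 1: can such a woman pass the entry rules as written?** Take a fertile woman aged 18 to 40 who uses contraception and has an early pregnancy with no signs.

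| Safeguard | Does it stop her before the first dose? |
|---|---|
| Exclusion list | No. Pregnancy is not named. |
| Contraception requirement | No. It lowers the chance of conception but does not detect an existing pregnancy. |
| βHCG on clinical doubt | No. There is no doubt to trigger it. |
| Baseline physical examination | Not reliably, in an early pregnancy without signs. |
| Baseline laboratory tests | Not as described. Their stated purpose is to find comorbid or uncompensated conditions, and βHCG is not named. The panel is not itemised, so it might be there. |
| Removal of women who become pregnant | No. It acts only once a pregnancy is known. |

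Exclusion of a *known* pregnancy is implied by the contraception and removal rules. The gap concerns unrecognised pregnancy only.

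**Step 2: would doubt arise soon after dosing starts?** Visits are three times weekly in the acute phase and weekly in maintenance, which shortens any exposure. However, the Introduction lists nausea, dizziness and drowsiness as common effects of ketamine, and Intervention provides ondansetron for nausea and vomiting. Early symptoms of pregnancy could be put down to the study drug.

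**Step 3: size.** The protocol gives no figure to reproduce. It states neither how many participants will be fertile women nor how often an unrecognised pregnancy occurs. Both inputs below are assumptions.

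- n = number of fertile women: 44, 66 or 88 (50%, 75% or 100% of the 88 patients)
- p = chance per woman of an unrecognised pregnancy at entry: 0.1%, 0.5% or 1%
- Expected number = n × p
- Chance of at least one = 1 − (1 − p)^n

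| n | p = 0.1% | p = 0.5% | p = 1% |
|---|---|---|---|
| 44 | 0.044; 4.3% | 0.22; 19.8% | 0.44; 35.7% |
| 66 | 0.066; 6.4% | 0.33; 28.2% | 0.66; 48.5% |
| 88 | 0.088; 8.4% | 0.44; 35.7% | 0.88; 58.7% |

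Each cell gives the expected number, then the chance of at least one. For the middle cell: 66 × 0.005 = 0.33, and 1 − 0.995^66 = 28.2%. Fewer than one case is expected in every cell.

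**The case against.** The strongest objection is that this is a journal article and the full protocol is not shown. No individual laboratory test is named, so the absence of βHCG from an unlisted panel is weak evidence that it is not done. The βHCG sentence also stands between a continuing contraception duty and a rule for pregnancies arising during the study. It can therefore be read as a for-cause test on study that says nothing about screening, and the article does not say that βHCG is done only on doubt.

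Part of this stands. A routine baseline βHCG cannot be ruled out, which limits confidence in the point. It does not remove the point, because the article is not silent: it sets out when βHCG is ordered and makes that conditional on doubt. If every fertile woman were tested at baseline, it would be odd to describe the supplementary test and leave out the main one.

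It is also fair to say that the size rests wholly on assumptions, that the upper end needs all 88 participants to be fertile women at the highest assumed rate, and that the documents give no estimate of fetal harm. Contraception, the baseline examination and frequent visits reduce the risk further. These arguments keep the point modest. They do not close the gap before the first dose.

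**Conclusion.** The concern holds. Followed as written, the entry rule lets an unsuspected early pregnancy be randomised and dosed in either arm, which is out of line with the protocol's own rule of removal and referral. On the assumed inputs the chance of at least one such case runs from 4.3% to 58.7%, with 28.2% in the middle scenario, and always with fewer than one case expected. That range shows only that the risk is not negligible; it is not an estimate for this trial.

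Confidence is medium because the laboratory panel is not itemised. The point concerns patient safety only; efficacy conclusions are unaffected. It calls for a cheap precaution that should be taken and is not a major defect.

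**What to change.** 1. Add pregnancy at entry to the exclusion criteria.
2. Require a negative βHCG from every fertile woman, run with the PI laboratory tests and as close to randomisation as practical. PI lasts about two weeks, and a test early in it can miss a very recent conception.
3. Keep the test on clinical doubt and the removal rule for conception during treatment. A single entry test does not cover later conception.
4. If βHCG is already in the baseline panel, say so; then only the wording changes.
5. The study is already running. If no baseline βHCG was done, offer fertile women already enrolled one test at a scheduled visit. This is secondary to the entry rule.

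**Cost:** one assay per fertile woman, at most 88 among randomised patients, plus an amendment. The number of candidates screened and the price of the assay are not given. No extra visit is needed, and sample size and analysis do not change. For women already enrolled the test is an added procedure, because Table 1 places clinical tests at baseline only.
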